## Appendix F

### Dose Modifications, Interruptions, and Delays (cont.)

**Table F3**  
Dose Adjustments for Neutropenia and Thrombocytopenia

| Dose Adjustment for Low Absolute Neutrophil Count |                                                                                               |
|---------------------------------------------------|-----------------------------------------------------------------------------------------------|
| ANC                                               | Pegasys Dose Reduction                                                                        |
| < 750 cells/mm                        | Reduce Pegasys to 135 µg                                                                      |
| < 500 cells/mm                        | Withhold Pegasys until ANC > 750 cells/mm  ,
reinstitute at 90 µg, and monitor |
| Dose Adjustment for Low Platelet Count            |                                                                                               |
| Platelet Count                                    | Pegasys Dose Reduction                                                                        |
| < 50,000 cells/mm                     | Reduce Pegasys to 90 µg                                                                       |
| < 25,000 cells/mm                     | Withhold treatment and conduct weekly or
more frequent monitoring                          |

ANC = absolute neutrophil count.

**Table F4**  
Dose Adjustment for Low Hemoglobin

|                                                              | One Level Adjustment for Copegus if: | Withhold Copegus if:  |
|--------------------------------------------------------------|--------------------------------------|-----------------------|
| In patients without
significant cardiovascular
disease | Hemoglobin < 10 g/dL                 | Hemoglobin < 8.5 g/dL |

### COPEGUS DOSE MODIFICATIONS

It is important that patients receive as close to the full dose of Copegus as possible. However, moderate or severe adverse reactions (clinical and/or laboratory) may necessitate a dose modification of Copegus. It is therefore recommended that the Copegus dose be reduced in gradual stepwise decrements as depicted in [Table F5](#).

## Appendix F

### Dose Modifications, Interruptions, and Delays (cont.)

**Table F5**  
General Copegus Dose-Reduction Scheme

|                       | Baseline Body Weight                       |                                            |
|-----------------------|--------------------------------------------|--------------------------------------------|
|                       | ≥ 75 kg                                    | < 75 kg                                    |
| Full Copegus dose     | 1200 mg/day
(AM: 3 tabs;
PM: 3 tabs) | 1000 mg/day
(AM: 3 tabs;
PM: 2 tabs) |
| One-level reduction   | 1000 mg/day
(AM: 3 tabs;
PM: 2 tabs) | 800 mg/day
(AM: 2 tabs;
PM: 2 tabs)  |
| Two-level reduction   | 800 mg/day
(AM: 2 tabs;
PM: 2 tabs)  | 600 mg/day
(AM: 2 tabs;
PM: 1 tab)   |
| Three-level reduction | 600 mg/day
(AM: 2 tabs;
PM: 1 tab)   | 400 mg/day
(AM: 1 tab;
PM: 1 tab)    |

At the discretion of the investigator, patients who experience a substantial hemoglobin decrease during treatment should have weekly or biweekly hematologic testing and clinical evaluation. Patients who have > 3 g/dL decrease from baseline in their Hgb concentration should have an appropriate work-up for anemia—including reticulocyte count—and a search for sources of bleeding.

If deemed necessary by the investigator, patients should be assessed at a minimum every 2 weeks until the AE is resolved or the patient is stable. Persistent adverse reactions may require two- or three-level dose reductions or necessitate that the dose be temporarily withheld.

Once the Copegus dose has been reduced or withheld for an adverse reaction, an attempt may be made to restart Copegus and/or increase the dose if the event has resolved or improved, at the discretion of the investigator. The Copegus dose should be increased in 200-mg increments by increasing the number of tablets taken daily in a stepwise manner until the desired level is achieved. It is not recommended to escalate to the fully prescribed dose of Copegus.

## **Appendix G**

### **Management of Specific Adverse Events and Laboratory Abnormalities**

#### **RENAL ABNORMALITIES**

If RO5024048 is discontinued because of renal abnormalities, the following measures will be performed as soon as possible:

- Blood measurements
  - Complete blood count with differential and peripheral smear for schistocytes
  - Chemistry with calculated creatinine clearance
- Blood pressure measurements
- Urine panel
  - Urinalysis (dipstick and microscopic)
  - Urine chemistry (first void of the day, chilled sample) for protein, creatinine, and microalbumin (for details and calculation of urine protein/creatinine ratio when urine protein is reported as undetectable)
  - Repeat urinalysis to confirm the presence of hematuria at the time of the additional evaluation (for hematuria only)
  - Repeat urine analysis to evaluate for leukocytes and the presence of infection (for hematuria only)
  - Urine culture and sensitivity (for hematuria only)
  - Urine protein electrophoresis
- Nephrology consultation
- Renal ultrasound or renal biopsy, if indicated per consultant evaluation

The investigator will use the additional clinical and laboratory measures to evaluate the relationship between renal abnormalities and other potential clinical findings and will contact the Roche Medical Monitor within 24 hours for further discussion. All events should be appropriately monitored (including obtaining laboratory test) until resolution or return to baseline.

#### **ELEVATED BLOOD PRESSURE/DECREASED RENAL FUNCTION**

During RO5024048 treatment and for 2 weeks thereafter, patients with elevations in systolic blood pressure of > 160 mmHg and diastolic blood pressure of > 100 mmHg confirmed (preferably within 1 week) or increases of 30 mmHg systolic or 20 mmHg diastolic from baseline will be scheduled for weekly blood pressure measurements and laboratory procedures described below.

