The absolute and percentage changes from baseline in vital sign parameters will be computed, and potentially serious changes will be noted. Electrocardiogram interval measurements will be summarized by nominal time. Appropriate summary statistics will be provided for all vital sign parameters. For a change from baseline in any vital sign parameter to be considered potentially serious, the change must be an increase or decrease of > 20% in the direction of worsening, and the absolute value must be outside the corresponding reference range as shown below:

- Systolic BP < 85 or > 180 mmHg OR diastolic BP > 110 mmHg
- Heart rate < 45 or > 120 beats per minute

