## Appendix A (cont'd) Schedule of Assessments

---

|   |                                                                                                                                                                                                                                                                                                                                                                                                                             |
|---|-----------------------------------------------------------------------------------------------------------------------------------------------------------------------------------------------------------------------------------------------------------------------------------------------------------------------------------------------------------------------------------------------------------------------------|
| o | Systolic and diastolic blood pressure and pulse.                                                                                                                                                                                                                                                                                                                                                                            |
| p | Body weight.                                                                                                                                                                                                                                                                                                                                                                                                                |
| q | Complete blood count with differential (RBC count, Hgb, hematocrit, MCV, MCH, MCHC, leukocytes, neutrophils, basophils, eosinophils, monocytes, lymphocytes, reticulocytes, platelets, haptoglobin); coagulation panel (PT/INR).                                                                                                                                                                                            |

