## **Appendix G**

### **Management of Specific Adverse Events and Laboratory Abnormalities (cont.)**

During RO5024048 treatment and for 2 weeks thereafter, patients with confirmed (preferably within 1 week) CRCL < 70 mL/min (< 1.17 mL/sec) but  $\geq$  60 mL/min ( $\geq$  1 mL/sec) OR a decrease from baseline  $\geq$  25% but < 35% OR urine protein/creatinine ratio  $\geq$  0.4 ( $\geq$  45.25 mg/mmol) but < 0.5 (< 56.51 mg/mmol) will be scheduled for weekly visits and laboratory assessments described below.

- Blood measurements
  - Complete blood count with differential and peripheral smear for schistocytes
  - Chemistry with calculated creatinine clearance
- Urine panel
  - Urinalysis (dipstick and microscopic)
  - Urine chemistry (first void of the day, chilled sample) for protein, creatinine and microalbumin (for details and calculation of urine protein/creatinine ratio when urine protein is reported as undetectable)

The investigator will use the additional clinical and laboratory measures to evaluate the relationship between elevated blood pressure findings/renal abnormalities and other potential clinical findings and will contact the Medical Monitor within 24 hours for further discussion. All events should be appropriately monitored (including obtaining laboratory test) until resolution or return to baseline.

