| Hypertension                                                                 |                                                                           |                                                                                                                             |                                                                                                                            |                                                                                                                                            |
| Adult > 17 years
(with repeat
testing at same
visit)      | > 140 – 159 mmHg
systolic

OR

> 90 – 99 mmHg
diastolic | > 160 – 179 mmHg
systolic

OR

> 100 – 109 mmHg
diastolic                                                 | > 180 mmHg systolic

OR

> 110 mmHg diastolic                                                                  | Life-threatening
consequences (e.g.,
malignant hypertension)
OR Hospitalization
indicated (other than
emergency room visit) |
| Pediatric ≤ 17
years
(with repeat
testing at same
visit) | NA                                                                        | 91 st – 94 th percentile
adjusted for age,
height, and gender
(systolic and/or
diastolic) | ≥ 95 th percentile
adjusted for age, height,
and gender (systolic
and/or diastolic)                    | Life-threatening
consequences (e.g.,
malignant hypertension)
OR Hospitalization
indicated (other than
emergency room visit) |
| Hypotension                                                                  | NA                                                                        | Symptomatic,
corrected with oral
fluid replacement                                                                    | Symptomatic, IV fluids
indicated                                                                                        | Shock requiring use of
vasopressors or
mechanical assistance
to maintain blood
pressure                                        |

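### Appendix G's absolute blood-pressure trigger joins its systolic and diastolic limits with 'and', so some patients with raised baseline pressure can reach Grade 3 hypertension without the weekly checks

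*Protocol*

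**What the plan says.** Appendix G, under Elevated Blood Pressure/Decreased Renal Function, sets a trigger with two limbs.

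- **Absolute limb:** systolic pressure "> 160 mmHg and diastolic blood pressure of > 100 mmHg confirmed (preferably within 1 week) or increases of 30 mmHg systolic". The systolic and diastolic limits are joined by 'and'.
- **Change limb:** "or increases of 30 mmHg systolic or 20 mmHg diastolic from baseline". Here the two are joined by 'or'.

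A patient who meets either limb has weekly blood-pressure measurements and a laboratory set: blood count with a peripheral smear for schistocytes, chemistry with creatinine clearance, and a urine panel. The investigator also "will contact the Medical Monitor within 24 hours for further discussion".

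Comparable rules elsewhere in the protocol use 'or':

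- The renal trigger that follows in Appendix G: "25% but < 35% OR urine protein/creatinine ratio".
- Grade 3 adult hypertension in Appendix I: "> 180 mmHg systolic" or "> 110 mmHg diastolic".
- The absolute vital-sign limits in Section 6.5: "Systolic BP < 85 or > 180 mmHg OR diastolic BP > 110 mmHg".

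The exclusion criteria in Section 4.1.2 set no blood-pressure limit.

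**The concern.** Read literally, the absolute limb ignores an isolated systolic or isolated diastolic elevation, however high, unless the change limb also fires. The change limb needs a large rise, so it is weakest in patients who enter with raised pressure. Such patients are free to enrol.

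Section 1.2.1 shows why this matters for RO5024048. Monkeys developed microangiopathic glomerulopathy, and their cardiac abnormalities were thought possibly secondary to renal hypertension. The Appendix G trigger is the rule that turns a high pressure reading into closer renal and hematologic follow-up. Scheduled visits from Week 4 to Week 24 are 4 weeks apart, so a missed patient can go without up to three weekly checks in each interval. The scheduled hematology panel (Appendix A, footnote q) does not include the schistocyte smear.

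**Working it through.** The protocol gives no figure to reproduce here, so the check is on the logic of the rule, in whole mmHg.

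**Inputs.** Trigger limits: Appendix G. Grade 2 hypertension (> 160 systolic or > 100 diastolic) and Grade 3 (> 180 or > 110): Appendix I. Potentially serious change (> 20% worsening together with > 180 systolic or > 110 diastolic): Section 6.5. Visit weeks: Appendix A.

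**Rule as written.** With baseline S0/D0 and follow-up S/D, the trigger fires if (S > 160 and D > 100), or S − S0 ≥ 30, or D − D0 ≥ 20. An increase of 30 or 20 is read as at least that much.

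**Lowest baseline from which a new event can be missed.** This is the smallest qualifying value minus the largest rise that does not fire the change limb.

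| New event | Smallest value | Largest silent rise | Lowest baseline missed |
|---|---|---|---|
| Grade 3 systolic | 181 | 29 | 181 − 29 = 152 |
| Grade 3 diastolic | 111 | 19 | 111 − 19 = 92 |
| Grade 2 systolic | 161 | 29 | 161 − 29 = 132 |
| Grade 2 diastolic | 101 | 19 | 101 − 19 = 82 |

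A systolic miss also needs D ≤ 100 and a diastolic rise below 20. A diastolic miss also needs S ≤ 160 and a systolic rise below 30. The systolic Grade 3 gap widens with baseline: from 152 only 181 is missed, from 155 the values 181–184, and from 160 the values 181–189. From 151 or lower, every Grade 3 systolic value is a rise of at least 30 and fires.

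**Example 1: 155/88 to a confirmed 183/96.** Grade 3, since 183 > 180. Absolute limb: 96 is not > 100. Change limb: 183 − 155 = 28 and 96 − 88 = 8. Nothing fires.

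**Example 2: 140/92 to 150/111.** Grade 3, since 111 > 110. Absolute limb: 150 is not > 160. Change limb: 150 − 140 = 10 and 111 − 92 = 19. Nothing fires. Section 6.5 would flag this patient: 19/92 = 20.7%, and 111 > 110.

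**Overlap with Section 6.5.** Three diastolic rises are potentially serious there yet stay below 20 mmHg: 92 to 111 (20.65%), 93 to 112 (19/93 = 20.43%) and 94 to 113 (19/94 = 20.21%). From 95 the figure is 19/95 = 20.0%, which is not > 20%. There is no systolic case: a rise of at most 29 exceeds 20% only from a baseline below 29/0.20 = 145, and 144 + 29 = 173 is not > 180.

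**What 'and' does to the absolute limb.** From a baseline systolic of 131 or less, any value > 160 is already a rise of at least 30. From a baseline diastolic of 81 or less, any value > 100 is already a rise of at least 20. The absolute limb thus adds something only for raised baselines. With 'and', it does so only when baseline systolic is ≥ 132, baseline diastolic is ≥ 82, and both limits are then crossed.

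**Rule with 'or'.** Every S > 180 exceeds 160 and every D > 110 exceeds 100, so no Grade 3 value can escape. An enumeration over baselines of 100–180 systolic and 60–110 diastolic, with follow-up values from baseline up to 199 and 120, confirms this. It gives the same 152 and 92 boundaries under 'and', and no misses under 'or'.

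**The case against.** The arithmetic is not in dispute on a literal reading. The case against rests on significance.

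- **Other monitoring continues.** Vital signs, chemistry with creatinine clearance and urine protein/creatinine are scheduled at every treatment visit. Scheduled tests also include platelets, reticulocytes, haptoglobin and lactate dehydrogenase, which bear on microangiopathic hemolysis. Renal triggers, stopping rules and adverse event reporting run independently. This stands, and it limits the loss. It does not replace the mandated weekly checks, the smear or the 24-hour contact.
- **A drug effect should appear as a rise from baseline, which the change limb detects.** This is largely true. What escapes is a smaller rise in someone already hypertensive, and at the edge of the gap only one value is missed.
- **The parallel with Section 6.5 is partial.** That rule also requires a > 20% worsening, and Example 1 (28/155 = 18.1%) does not meet it. This is correct. The parallel is only that its systolic and diastolic limits are alternatives.
- **Appendix I grading requires repeat testing at the same visit.** The examples assume it was done.
- **'And' can be read as listing two separate elevations.** It can. But the same sentence uses 'or' for the change limb, and a safety trigger that sites may read in two ways also needs correcting.
- **The fix has a burden.** A patient stable at 162/85 would qualify for weekly checks throughout. With 8 scheduled visits through Week 24, that is up to 24 − 8 = 16 additional weekly visits, plus the 2 weeks after treatment. This is a real cost, but the present rule already accepts it for patients stable above both limits.

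**Conclusion.** The concern holds. As written, the trigger misses new Grade 3 hypertension in two regions: baseline systolic ≥ 152 mmHg, and baseline diastolic ≥ 92 mmHg, in each case with the other pressure below its limits. New Grade 2 values can be missed from baselines of 132 systolic or 82 diastolic. The conclusion rests on the literal reading of 'and', on whole-mmHg values, and on the absence of any entry cap on blood pressure. The protocol does not give the baseline pressure distribution, so the number of patients affected cannot be stated and may be small. The defect is confined to safety monitoring. The SVR-12 analysis, the randomization and the stopping rules are unaffected.

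**What to change.** In Appendix G, Elevated Blood Pressure/Decreased Renal Function, change the absolute limb to systolic > 160 mmHg **or** diastolic > 100 mmHg, confirmed (preferably within 1 week). Leave the 30/20 mmHg change limb and Section 6.5 as they are.

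The change is one word and uses only procedures already in Appendix G. Its cost is weekly pressure and laboratory checks, during RO5024048 treatment and for 2 weeks after, for some further patients, including some whose high pressure is long-standing and stable. How many cannot be estimated from the protocol.

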## **Appendix G**

### **Management of Specific Adverse Events and Laboratory Abnormalities (cont.)**

During RO5024048 treatment and for 2 weeks thereafter, patients with confirmed (preferably within 1 week) CRCL < 70 mL/min (< 1.17 mL/sec) but  $\geq$  60 mL/min ( $\geq$  1 mL/sec) OR a decrease from baseline  $\geq$  25% but < 35% OR urine protein/creatinine ratio  $\geq$  0.4 ( $\geq$  45.25 mg/mmol) but < 0.5 (< 56.51 mg/mmol) will be scheduled for weekly visits and laboratory assessments described below.

- Blood measurements
  - Complete blood count with differential and peripheral smear for schistocytes
  - Chemistry with calculated creatinine clearance
- Urine panel
  - Urinalysis (dipstick and microscopic)
  - Urine chemistry (first void of the day, chilled sample) for protein, creatinine and microalbumin (for details and calculation of urine protein/creatinine ratio when urine protein is reported as undetectable)

The investigator will use the additional clinical and laboratory measures to evaluate the relationship between elevated blood pressure findings/renal abnormalities and other potential clinical findings and will contact the Medical Monitor within 24 hours for further discussion. All events should be appropriately monitored (including obtaining laboratory test) until resolution or return to baseline.

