#### **4.5.2.3 Assessments at Study Completion/Early Termination Visit**

Any patient who prematurely discontinues all study drugs should return for the PW Visit as soon as possible after the last dose of study medication. Additional requirements exist for patients who have unquantifiable HCV RNA levels at the time of premature study drug discontinuation (see [Appendix A](#)).

- If a patient stops Pegasys, all study medications must be discontinued.
- If a patient stops one DAA (either RO5024048 or boceprevir), the patient may remain on the other DAA (either RO5024048 or boceprevir) plus Pegasys/Copegus.
- If both RO5024048 and boceprevir are stopped, the patient may remain on Pegasys/Copegus.
- If a patient stops Copegus, all study medications must be discontinued.
- Patients should not be treated with a single DAA (either RO5024048 or boceprevir) and Pegasys or with Pegasys monotherapy.
- In other circumstances, the investigator should consult with the Sponsor.

See [Appendix A](#) for the Schedule of Assessments performed at the Study Completion/Early Termination Visit.

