#### **4.6.1.1 Discontinuation from Study Drug**

All study medications should be stopped for individual patients for any of the following reasons:

- Hepatitis C virus RNA titer > 100 IU/mL by Week 24
- Quantifiable HCV RNA at Week 24
- Hepatitis C virus RNA virologic breakthrough before the end of treatment with boceprevir and/or RO5024048/placebo and/or Pegasys/Copegus. Virologic breakthrough is defined as:

A sustained increase in HCV RNA of  $\geq 1 \log_{10}$  IU/mL ( $\geq 2$  consecutive measurements) while on boceprevir/RO5024048 compared with the on-treatment nadir (where the nadir is a  $\geq 1 \log_{10}$  IU/mL decrease from baseline after 2 weeks of treatment or  $\geq 2 \log_{10}$  IU/mL decrease from baseline after 4 weeks of treatment)

Confirmed quantifiable HCV RNA ( $\geq 25$  IU/mL by  $\geq 2$  consecutive measurements) in a patient who had been previously confirmed as having unquantifiable HCV RNA ( $< 25$  IU/mL by  $\geq 2$  consecutive measurements) before the end of treatment with boceprevir/RO5024048

Response ( $< 25$  IU/mL by  $\geq 2$  consecutive measurements) to boceprevir/RO5024048 treatment and subsequent quantifiable viral load ( $\geq 25$  IU/mL by  $\geq 2$  consecutive measurements) once boceprevir/RO5024048 treatment has been completed (but Pegasys/Copegus treatment continues)

- Hepatitis C virus partial response before the end of treatment with boceprevir/RO5024048/Pegasys/Copegus/placebo, defined as an initial HCV RNA decline ( $\geq 1 \log_{10}$  IU/mL decrease from baseline after 2 weeks of treatment or  $\geq 2 \log_{10}$  IU/mL decrease from baseline after 4 weeks of treatment) followed by stabilization ( $\geq 2$  consecutive measurements similar to those at nadir) while on boceprevir/RO5024048/Pegasys/Copegus/placebo treatment and/or a HCV RNA  $\geq 1000$  IU/mL by the end of boceprevir/RO5024048/Pegasys/Copegus/placebo treatment of at least 4 weeks in duration
- Any confirmed Grade 4 laboratory abnormality deemed clinically significant (based on the investigator's assessment)
- A positive troponin value ( $> 0.100$  ng/mL)

RO5024048 should be stopped for individual patients for any of the following reasons:

- A creatinine clearance decrease  $\geq 35\%$  from baseline or  $< 60$  mL/min ( $< 1.00$  mL/sec) confirmed by repeat test, preferably within 1 week

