### **5.3.5.4 Abnormal Laboratory Values**

Not every laboratory abnormality qualifies as an AE. A laboratory test result should be reported as an AE if it meets any of the following criteria:

- Accompanied by clinical symptoms
- Results in a change in study treatment (e.g., dosage modification, treatment interruption, or treatment discontinuation)
- Results in a medical intervention (e.g., potassium supplementation for hypokalemia) or a change in concomitant therapy
- Requires further diagnostic evaluation (e.g., an abnormal laboratory result requires a scan/radiologic work up, biopsy, etc., to further manage the case for diagnostic purposes)
- Clinically significant in the investigator's judgment

It is the investigator's responsibility to review all laboratory findings. Medical and scientific judgment should be exercised in deciding whether an isolated laboratory abnormality should be classified as an AE.

If a clinically significant laboratory abnormality is a sign of a disease or syndrome (e.g., alkaline phosphatase and bilirubin 5 times the ULN associated with cholecystitis), only the diagnosis (i.e., cholecystitis) should be recorded on the AE eCRF.

If a clinically significant laboratory abnormality is not a sign of a disease or syndrome, the abnormality itself should be recorded on the AE eCRF, along with a descriptor indicating if the test result is above or below the normal range (e.g., "elevated potassium," as opposed to "abnormal potassium"). If the laboratory abnormality can be characterized by a precise clinical term per standard definitions, the clinical term should be recorded as the AE. For example, an elevated serum potassium level of 7.0 mEq/L should be recorded as "hyperkalemia."

Observations of the same clinically significant laboratory abnormality from visit to visit should not be repeatedly recorded on the AE eCRF, unless the etiology changes. The initial severity of the event should be recorded, and the severity or seriousness should be updated any time the event worsens.

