#### **RO5024048 AND BOCEPREVIR DOSE INTERRUPTION OR DISCONTINUATION**

No dose modifications will be allowed for RO5024048 or boceprevir.

RO5024048 must be discontinued immediately and the Sponsor's Medical Monitor contacted within 24 hours if any of the following are confirmed and **considered related** to the study drug:

- Creatinine clearance:  $\geq 35\%$  decrease from baseline or  $< 60$  mL/min ( $< 1.00$  mL/sec) confirmed by repeat test, preferably within 1 week
- Any clinically significant Grade 4 laboratory abnormality confirmed by repeat test, preferably within 1 week, unless otherwise defined
- Any SAE assessed as related to RO5024048

It is important that patients receive the full dose of RO5024048 and/or boceprevir. However, moderate or severe adverse reactions (clinical and/or laboratory) may necessitate dose interruption or discontinuation of RO5024048 and/or boceprevir.

If a dose of RO5024048 or boceprevir is missed and the patient remembers the same day, the patient must take the missed dose if the next scheduled dose is more than 4 hours away. The patient should not take two doses at the same time or within 4 hours of each other.

Patients who discontinue all study drugs should return for the PW visit as soon as possible after their last dose of study medication, according to [Appendix A](#). Patients who prematurely discontinue from the study will be assessed for safety and efficacy at 4 and 12 weeks after the last dose of study treatment. In addition, patients who prematurely discontinue and have unquantifiable HCV RNA will be assessed for efficacy at 12 weeks after the last dose of study treatment as long as they remain HCV RNA unquantifiable at their last assessment.

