## Appendix H

### Urinary Protein Monitoring Plan (cont.)

**Table H1**  
Urinary Monitoring Plan for Protein

| Timepoint           | Finding                                                                    | Action Required by Investigator                                                                                                                                                                           |                                                                                                |
|---------------------|----------------------------------------------------------------------------|-----------------------------------------------------------------------------------------------------------------------------------------------------------------------------------------------------------|------------------------------------------------------------------------------------------------|
| Baseline to Week 24 | Urine chemistry protein/Cr ratio $\geq 0.5$ and greater than the baseline. | Confirm value with repeat urine measurement within 1 week                                                                                                                                                 |                                                                                                |
|                     |                                                                            | IF CONFIRMED:
Discontinue RO5024048 immediately. Collect urine for protein electrophoresis. Continue urine monitoring until protein/Cr ratio returns to baseline or stabilizes. Refer to nephrologist. | IF NOT CONFIRMED:
Continue therapy with RO5024048, continue urine assessments per protocol. |
| Weeks 24–60         | Urine chemistry protein/Cr ratio $\geq 0.5$ and greater than the baseline  | Collect urine for protein electrophoresis. Continue urine monitoring weekly until protein/Cr ratio returns to baseline or stabilized. Refer to nephrologist.                                              |                                                                                                |

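### In the two weeks after RO5024048 ends for a non-renal reason, some of the larger confirmed falls in creatinine clearance trigger neither Appendix G renal rule, although milder falls trigger weekly visits

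*Protocol*

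**What the plan says.** Four provisions bear on a fall in CRCL.

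- **Weekly-visit rule** (Appendix G, Elevated Blood Pressure/Decreased Renal Function). It applies during RO5024048 and for two weeks afterwards. The CRCL triggers are a confirmed value below 70 but at least 60 mL/min, or a percentage fall, continuing: "OR a decrease from baseline $\geq$ 25% but < 35% OR urine protein/creatinine ratio". A ratio of 0.4 to below 0.5 is the third trigger. The response is weekly visits with set blood and urine tests.
- **Stopping rule** (Section 4.6.1.1, repeated in Appendix F). The worse tier, a confirmed fall of at least 35% or a CRCL below 60, appears under this lead-in: "RO5024048 should be stopped for individual patients for any of the following reasons".
- **Work-up rule** (Appendix G, Renal Abnormalities). It covers blood, urine, electrophoresis and a nephrology consultation, and opens: "If RO5024048 is discontinued because of renal abnormalities, the following measures will be performed as soon as possible".
- **Urine protein** (Appendix H, Table H1). For Weeks 24–60, a ratio of 0.5 or more and above baseline has its own row: "Continue urine monitoring weekly until protein/Cr ratio returns to baseline or stabilized. Refer to nephrologist". CRCL has no such row.

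RO5024048 ends at Week 24 in both arms (Section 4.3.2). It can also end earlier while other drugs go on. After one direct-acting antiviral is stopped, Section 4.5.2.3 says "the patient may remain on the other DAA (either RO5024048 or boceprevir) plus Pegasys/Copegus".

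**The concern.** The ceilings on the weekly-visit rule make sense only while there is a drug to stop. During treatment, a patient who passes the ceiling goes to the stopping rule and from there to the work-up. After the drug has ended on schedule, or for a reason unrelated to the kidney, there is nothing left to stop and the work-up's opening condition cannot be met. The ceilings still apply in those two weeks, so response and severity can run in opposite directions.

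The two-week tail is there for a reason. Glomerular toxicity in monkeys is a nonclinical signal for this drug (Section 1.2.1), and the tail extends renal monitoring just past the last dose.

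Three routes lead into the gap:

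- the Week 24 chemistry sample, whose confirming repeat falls after the drug has ended;
- the premature-withdrawal visit;
- routine chemistry within two weeks of stopping RO5024048 alone for a non-renal reason.

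**Working it through.** **Inputs.** The weekly-visit limits are from Appendix G and the stop-tier limits from Section 4.6.1.1. Screening CRCL must exceed 70 mL/min (Section 4.1.2, exclusion 19); baseline is assumed to exceed 70 as well. The plan states no figure to reproduce, because this is a check of rule logic.

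Let b be baseline CRCL, C the confirmed value after RO5024048, and f = (b − C)/b.

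- Weekly rule met (CRCL limbs): 60 ≤ C < 70, or 0.25 ≤ f < 0.35.
- Worse tier: f ≥ 0.35, or C < 60.

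**Uncovered values (worse tier met, weekly rule not met).**

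- If f ≥ 0.35, the percentage limb fails. The value is caught only if 60 ≤ C < 70, so it is missed at C ≥ 70 and at C < 60.
- If C < 60 and f < 0.35, the absolute limb fails. The value is caught only if f ≥ 0.25, so it is missed at f < 0.25.

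The gap is therefore (f ≥ 0.35 with C ≥ 70) or (C < 60 with f < 0.25 or f ≥ 0.35). A grid of baselines from 70.1 to 200 and values from 20 up to baseline gives the same set with no mismatch.

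**Where it can occur.**

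- f ≥ 0.35 with C ≥ 70 needs b ≥ 70/0.65 = 107.7.
- C < 60 with f < 0.25 needs b < 60/0.75 = 80.
- From b = 60/0.65 = 92.3 upward, every C < 60 is uncovered.

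**Examples.**

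| Baseline | Confirmed CRCL | Fall | Weekly visits by CRCL? |
|---|---|---|---|
| 120 | 85 | 29.2% | yes |
| 120 | 75 | 37.5% | no |
| 100 | 70 | 30.0% | yes |
| 100 | 63 | 37.0% | yes (60 to < 70) |
| 100 | 55 | 45.0% | no |
| 85 | 59 | 30.6% | yes (25% to < 35%) |
| 75 | 62 | 17.3% | yes |
| 75 | 58 | 22.7% | no |
| 75 | 55 | 26.7% | yes |
| 75 | 48 | 36.0% | no |

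At baseline 120 (0.75 × 120 = 90; 0.65 × 120 = 78), the response alternates as CRCL falls: weekly visits from 90 down to just above 78, nothing from 78 to 70, weekly visits from below 70 to 60, nothing below 60.

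**Time to the next scheduled chemistry.** Assume that the Week 24 visit is at the end of RO5024048 and the repeat is at about Week 25. In Arm A the next chemistry is at follow-up Week 4: 24 + 4 − 25 = 3 weeks away. In Arm B it is at Week 30: 30 − 25 = 5 weeks away.

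**Weekly visits lost.** The protocol does not say when weekly visits end. If they stop with the two-week window, about one (Week 26) or two are lost. If they ran until resolution, two would be lost in Arm A (Weeks 26 and 27) or four in Arm B (Weeks 26–29) before the next scheduled chemistry.

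**The case against.** The strongest reply is that the patient is not unprotected.

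- **Adverse event rules.** Section 5.3.5.4 says "A laboratory test result should be reported as an AE if it meets any of the following criteria", and those criteria include a need for further diagnostic evaluation and clinical significance in the investigator's judgment. Section 5.5.1 then requires follow-up to resolution or stability.
- **Other triggers.** Blood pressure is an independent entry in the same two weeks: "increases of 30 mmHg systolic or 20 mmHg diastolic from baseline will be scheduled for weekly blood pressure measurements". A ratio of 0.4 to below 0.5 brings weekly visits, and 0.5 or more falls under Table H1.
- **Existing monitoring.** A patient already on weekly visits for a milder value is being watched, and scheduled chemistry includes the CRCL calculation.
- **Package inserts.** Section 5.1.1 also refers management of renal parameters to the boceprevir, Pegasys and Copegus inserts. Arm B patients after Week 24, and those who stopped RO5024048 alone, are still taking those drugs.

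All of this stands. A reader might infer that such patients have only general adverse event follow-up. The documents do not support that, because of the other triggers and because the inserts, not reproduced here, may cover patients still on the other drugs. A reader might also infer that renal monitoring fails during treatment; it does not, because the stopping rule and work-up take over there.

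An investigator is also unlikely to watch a 45% fall less closely than a 30% fall. That limits the harm but leaves the text uncorrected. None of these provisions is a CRCL trigger in Appendix G for a panel, a weekly schedule or a nephrology consultation. The protocol considered a panel and weekly schedule necessary for milder falls in the same two weeks.

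**Conclusion.** The rule is wrong as written, and the point is minor. In the two weeks after RO5024048 has ended by completion or for a non-renal reason, the CRCL values derived above meet neither Appendix G renal rule, while milder values bring weekly visits and a fixed panel. Table H1 closes the same hole for urine protein at Weeks 24–60, which suggests an oversight.

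The practical loss is the panel, a written nephrology trigger and about one or two weekly visits, taking the visits to end with the two-week window. The number of patients is not in the protocol and is assumed to be small.

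A reader might infer that every fall past the stopping threshold is missed. That is not so: a drop from 100 to 63, or from 85 to 59, is caught by the other limb. Nor does the gap affect an endpoint or show that patients were harmed. Section 1.2.1 reports no clinical renal injury with up to 24 weeks of dosing.

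**What to change.** In Appendix G, add that once RO5024048 has ended the upper limits no longer apply. Any confirmed CRCL below 70 mL/min, or fall of 25% or more, then gets the weekly visits and panel. Add that a fall of at least 35%, or a CRCL below 60, gets the Renal Abnormalities work-up and nephrology consultation whatever the reason the drug ended, in the way Table H1 handles a ratio of 0.5 or more.

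This leaves no uncovered value: C < 60 implies C < 70, and f ≥ 0.35 implies f ≥ 0.25. The cost is two sentences, using tests and referrals already in the protocol. The downside is a few extra visits and referrals in few patients.
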